### Statistical analyses

Descriptive statistics will be generated for all socio-demographic and clinical characteristics and outcome measures. Chi-square tests, independent samples *t* tests (in case of normality of the measure) and Mann-Whitney *U* tests (in case of non-normality of the measure) will be used to analyse whether randomisation resulted in comparable patient groups. A *p* value of <0.05 will be considered significant. Analyses will be performed using IBM SPSS Statistics version 22 (IBM, Armonk, NY, USA) and Stata version 12.1 (StataCorp, College Station, TX, USA) software.

To investigate the efficacy of Oncokompas, linear mixed-effect models will be used to compare longitudinal changes in outcome measures for efficacy in both groups over time (intention-to-treat analyses). Independent samples *t* tests will be used to measure differences between the intervention and control groups at follow-up assessments. Cohen’s *d* [46] will be calculated as a measure of effect size (ES) for intervention group versus control group. Cohen’s *d* is computed as the difference between two means, divided by the pooled SD. The magnitude of the ES is classified as large (≥0.80), moderate (0.50–0.79) or small (<0.50) [47].

To investigate associations of the reach of Oncokompas within this RCT, chi-square tests, independent samples *t* tests and Mann-Whitney *U* tests will be used to analyse whether there are differences between participants and non-participants in the follow-up study (part 2) regarding baseline characteristics (part 1).

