### Study design

The study is introduced to eligible cancer survivors as a baseline study (part 1) and a follow-up study (part 2). Study information is given and informed consent is requested for both parts separately. Cancer survivors who fulfil the inclusion criteria and not the exclusion criteria for the first part are asked to participate in the baseline study. Baseline assessment (T0) will take place after the first informed consent form is signed. After completion of the baseline assessment, participants who fulfil the inclusion criteria and not the exclusion criteria for the second part are asked to participate in the follow-up study. After the second informed consent is given, participants will be randomly allocated to one of the two study arms. Follow-up assessments will take place post-intervention (T1) and at 3-month (T2) and 6-month (T3) follow-up. In the intervention group, T1 assessment takes place 1 week after completion of Oncokompas or 2 weeks after inclusion when Oncokompas is not completed. In the control group, T1 assessment takes place 2 weeks after inclusion. Participants allocated to the control group obtain access to Oncokompas after completion of the T3 assessment. A flowchart of the RCT is shown in Fig. 1, and the schedule of enrolment, interventions and assessments (according to SPIRIT guidelines) is provided in Fig. 2.

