### Outcome assessment

The primary outcome measure to assess efficacy of Oncokompas is patient activation. Secondary outcome measures include self-efficacy, personal control, perceived patient-physician interaction, mental adjustment to cancer, need for supportive care and HRQOL. Furthermore, cost-utility outcomes will be assessed. *Reach* is defined as the percentage of cancer survivors who get access to Oncokompas within the context of this RCT. To obtain insight into possible factors associated with reach, we will obtain data on socio-demographic and clinical characteristics, health literacy, health locus of control (HLC), Internet use, attitude towards eHealth and the outcome measures on efficacy.

Primary and secondary outcome measures to measure efficacy are collected at baseline, post-intervention and at 3- and 6-month follow-up. Cost-utility outcomes are collected at baseline and at 3- and 6-month follow-up. Outcome measures to investigate associations of reach are collected at baseline. An overview of the outcome measures is presented in Table 1.

**Table 1 Tab1:** Study outcome measures and instruments

Outcome measure	Instrument
Efficacy^a^	
Primary outcome measure	
Patient activation	Patient Activation Measure (PAM)
Secondary outcome measures	
Self-efficacy	General Self-Efficacy Scale (GSE)
Personal control	Pearlin Mastery Scale (PMS)
Perceived patient-physician interaction	Five-item Perceived Efficacy in Patient-Physician Interactions (PEPPI-5)
Need for supportive care	34-item Short Form Supportive Care Needs Survey (SCNS-SF34) and head and neck cancer-specific module (SCNS-HNC)
Mental adjustment to cancer	Mental Adjustment to Cancer Scale (MAC)
Health-related quality of life	EORTC QLQ-C30
	EORTC QLQ-BR23
	EORTC QLQ-CR29
	EORTC QLQ-H&N43
	EORTC QLQ-HL27
	EORTC QLQ-NHL-LG20
	EORTC QLQ-NHL-HG29
Cost-utility measures^b^	
Outcome measures on cost-utility	
Quality-adjusted life-years	5 dimension EuroQol questionnaire (EQ-5D)
Medical costs	iMTA Medical Consumption Questionnaire (iMCQ)
Productivity costs	iMTA Productivity Cost Questionnaire (iPCQ)
Reach^c^	
Associations of reach	
Health literacy	Functional, Communicative and Critical Health Literacy scales (FCCHL)
Health locus of control	Multidimensional Health Locus of Control (MHLC)
Internet use	Adapted version of van de Poll-Franse and Van Eenbergen questionnaire [44]
Attitude towards eHealth	e-Health Impact Questionnaire (eHIQ)

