### Sample size

To demonstrate presence of an effect between T3 and T0 of at least 0.5 standard units as statistically significant in a one-tailed test at α = 0.05 and a power of (1 − β) = 0.80, a minimum of 51 participants per arm in each condition will be required at follow-up. Anticipating a drop-out rate of 25% between T0 and T3, 68 participants per condition arm per tumour type need to be included at T0. The total study cohort thus comprises 544 cancer survivors representing 136 cancer survivors per tumour type (breast, colorectal, and head and neck cancer or lymphoma).

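### The efficacy mixed models state no adjustment for the pre-randomisation T0 score; on the ordinary reading they give up precision that could be had at no cost

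*Protocol article*

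**What the plan says.** All references are to the protocol article.

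- **Primary outcome (Outcome assessment):** "The primary outcome measure to assess efficacy of Oncokompas is patient activation". It is measured at T0, T1, T2 and T3.
- **Timing (Study design):** "Baseline assessment (T0) will take place after the first informed consent form is signed". Then: "After the second informed consent is given, participants will be randomly allocated to one of the two study arms". T0 is therefore a pre-randomisation measurement, held on everyone who is randomised.
- **Efficacy model (Statistical analyses):** "linear mixed-effect models will be used to compare longitudinal changes in outcome measures for efficacy in both groups over time". No covariate is named, and the text does not say how T0 enters the model.
- **Second comparison (same section):** "Independent samples *t* tests will be used to measure differences between the intervention and control groups at follow-up assessments". This does not use T0 either.
- **Target effect (Sample size):** "an effect between T3 and T0 of at least 0.5 standard units", "in a one-tailed test at α = 0.05 and a power of (1 − β) = 0.80". The section gives 51 per arm at follow-up for each tumour type, 68 after allowing for 25% drop-out, and 544 in total. It gives no correlation between T0 and follow-up, and does not say whether the standard unit is the SD of the score or of the change.

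**The concern.** A model that compares change over time between arms, with an effect framed as T3 against T0, is normally fitted as group by time with T0 among the responses and a separate T0 mean in each arm. The T3 effect is then a difference between mean changes.

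Because T0 precedes randomisation, the true arm difference at T0 is zero, and any observed difference is chance. A change contrast subtracts the whole of that chance difference, although T0 predicts only a share rho of it at T3. The remaining share, 1 − rho, stays in the estimate and favours the arm that happened to start lower. Over repeated randomisations this averages out, so what is lost is precision. Patient activation and every other efficacy outcome would carry a wider confidence interval than the collected data allow.

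**Working it through.** **1. The plan's own figure.** For 0.5 SD, one-sided 5% and 80% power, the normal approximation gives 50 per arm. The exact noncentral t gives 51 (power 0.806). Then 51/0.75 = 68, and 68 × 2 arms × 4 tumour types = 544. All three stated figures reproduce.

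**2. Variances.** Let the score SD be 1 at both visits, with complete data and n per arm.
- Difference in mean change: 2(1 − rho) × 2/n
- Difference adjusted for T0: (1 − rho²) × 2/n
- Ratio, adjusted over change: (1 − rho²) / [2(1 − rho)] = (1 + rho)/2
- Variance saved: (1 − rho)/2. Standard error saved: 1 − √[(1 + rho)/2]

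Rho is not in the article, so the range is an assumption.

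| rho | variance saved | standard error saved |
|---|---|---|
| 0.3 | 35% | 19% |
| 0.4 | 30% | 16% |
| 0.5 | 25% | 13% |
| 0.6 | 20% | 11% |
| 0.7 | 15% | 8% |
| 0.8 | 10% | 5% |

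**3. Does this carry over to a four-visit mixed model?** The generalised least squares variance of the T3 effect was computed with compound symmetry and 272 per arm, first with free T0 means and then with a common T0 mean.
- Complete data: 0.00882 against 0.00618 at rho 0.4 (30% saved); 0.00441 against 0.00375 at rho 0.7 (15% saved).
- 25% missing at T3 only: 0.01062 against 0.00797 at rho 0.4 (25% saved); 0.00536 against 0.00470 at rho 0.7 (12% saved).

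**4. Power at 51 per arm, one-sided 5%, if the standard unit is the score SD.** The standardised effects are 0.5/√[2(1 − rho)] for change and 0.5/√(1 − rho²) for the adjusted analysis, with power from the noncentral t.

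| rho | change | adjusted |
|---|---|---|
| 0.4 | 74% | 86% |
| 0.5 | 81% | 89% |
| 0.6 | 88% | 93% |
| 0.7 | 94% | 97% |

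**5. All tumour types pooled.** With 4 × 51 = 204 per arm at T3, power for 0.5 SD is at least 99.8% under either analysis for rho of 0.4 or more.

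**6. Interval width, for illustration at rho 0.5.** At 51 per arm the 95% half-width is 1.96 × √(1.00 × 2/51) = 0.39 SD for change and 1.96 × √(0.75 × 2/51) = 0.34 SD adjusted. At 204 per arm both halve, to about 0.19 and 0.17 SD.

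**The case against.** The strongest objection is that the article does not fix the model the concern assumes. It names no fixed effects, covariates or covariance structure. A mixed model with a common T0 mean also compares changes over time, and has essentially the precision of the covariate-adjusted model. How baseline enters the model is often left to an analysis plan, and none is shown. This stands in part: a reader might infer that the plan rules out T0 adjustment, and the text does not support that. But the article does go as far as naming the contrast, a comparison of changes, and the ordinary reading of that contrast is the less precise one.

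Three other stronger readings also fail.
- **Bias or an invalid test.** Under randomisation the change contrast is unbiased and its type I error is controlled. The shift after a chance T0 imbalance is conditional on that imbalance.
- **An underpowered trial.** Pooled power for 0.5 SD is near 100% either way. At 51 per arm the change contrast reaches the planned 80% from rho 0.5 upward. If the standard unit is the SD of the change, it has 80.6% power at 51 per arm whatever rho is.
- **A fixed percentage loss.** Every percentage depends on a correlation the article does not give. The larger figures are variances under complete data, whereas the plan expects 25% drop-out.

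**Conclusion.** The point holds as a free gain in precision. It does not show an error that threatens validity. T0 is measured before randomisation, no sentence adjusts for it, and on the ordinary reading the efficacy contrast is less precise than it need be at every rho considered.

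The size rests on three assumptions: rho between 0.3 and 0.8, equal variances at T0 and T3, and the group-by-time model with free T0 means. If the authors already intend a common T0 mean, there is no loss and a clause saying so settles the matter. The practical benefit is narrower intervals, better power for effects below 0.5 SD, and sharper estimates within tumour types, the level at which the sample size was set.

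**What to change.** In the Statistical analyses section, state that each efficacy mixed model takes T1, T2 and T3 as responses, with the T0 score as a covariate interacting with visit. Alternatively, state that T0 stays among the responses with a common mean across arms. Report the T3 arm difference, with its confidence interval, from that model. The article's definition of Cohen's d need not change for this.

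The cost is a change of wording. T0 is already collected from everyone randomised, so no extra data, visits or participants are needed.

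### Patient activation gets both a mixed model and raw t tests at the follow-up visits, all at p<0.05, with nothing saying which one decides

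*Protocol article*

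**What the plan says.** Under Statistical analyses, the article gives two inferential analyses for the same efficacy outcomes:

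- First, "linear mixed-effect models will be used to compare longitudinal changes in outcome measures for efficacy in both groups over time (intention-to-treat analyses").
- Then, independent samples t "tests will be used to measure differences between the intervention and control groups at follow-up assessments".

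One rule covers both: a p "value of <0.05 will be considered significant". The sidedness is not given. The t tests are not called descriptive, supportive or conditional on the model.

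The Sample size section has a more specific target: "an effect between T3 and T0 of at least 0.5 standard units", in a "one-tailed test at α = 0.05" with "power of (1 − β) = 0.80". Outcome assessment names patient activation (PAM) as the primary outcome without a time point. Study design lists T1, T2 and T3 as the follow-up assessments.

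Cohen's d is defined as a difference of two means over the pooled SD and is "classified as large (≥0.80), moderate (0.50–0.79) or small (<0.50"). The small band has no lower limit. Imputation is described only for costs and EQ-5D utilities, under Cost-utility analyses.

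**The concern.** The plan has one primary outcome but several tests of it. The mixed model addresses the whole course from T0. The t tests address the arm means visit by visit. The sample size addresses T3 against T0. These can give different answers, and the analysis section has no rule for that case.

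The t tests are also the poorer tool. Every participant gives a PAM score at T0, and a t test of follow-up means discards it. No imputation is stated for PAM, so each t test uses whoever responded at that visit, beside a model labelled intention-to-treat. If drop-out depends on earlier scores, the mixed model can use those scores and the raw t test cannot.

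At stake is the main efficacy claim. A favourable result could come from any of several tests, and a null result would still be labelled a small effect.

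**Working it through.** **1. The plan's own figures.** Inputs from Sample size: d = 0.5, one-sided alpha 0.05, power 0.80, drop-out 25%, two arms, four tumour types.

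- n per arm = 2(1.645 + 0.842)²/0.5² = 49.5, so 50 by the normal approximation. The exact t-test solution is 50.15, rounded up to **51**.
- 51/(1 - 0.25) = **68** per arm per tumour type.
- 68 × 2 × 4 = **544**.

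All three reproduce. Evaluable at T3: 51 per arm within one tumour type, or 4 × 51 = 204 per arm overall.

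**2. Precision.** The correlation r between PAM scores at different visits is not in the document. It is assumed equal between all visits and varied from 0.4 to 0.8. With the raw T3 comparison set to variance 1, a change-from-baseline contrast has variance 2(1 - r) and a baseline-adjusted contrast has 1 - r².

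| r | Change, 2(1-r) | Adjusted, 1-r² | Raw/adjusted |
|---|---|---|---|
| 0.4 | 1.20 | 0.84 | 1.19 |
| 0.5 | 1.00 | 0.75 | 1.33 |
| 0.6 | 0.80 | 0.64 | 1.56 |
| 0.7 | 0.60 | 0.51 | 1.96 |
| 0.8 | 0.40 | 0.36 | 2.78 |

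The raw t test loses to the adjusted contrast at any positive r. It loses to a plain change contrast only when r exceeds 0.5.

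**3. False positives if any nominal win counted.** Four correlated visits were simulated under the null with complete data and large-sample statistics (400,000 draws per r). The model test is the 3-df group-by-time test. The last column combines it with the two-sided t tests.

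| r | Three t tests, two-sided | Three t tests, one-sided | Model test or any t test |
|---|---|---|---|
| 0.4 | 0.131 | 0.124 | 0.156 |
| 0.5 | 0.126 | 0.118 | 0.155 |
| 0.6 | 0.119 | 0.112 | 0.152 |
| 0.7 | 0.108 | 0.101 | 0.144 |
| 0.8 | 0.098 | 0.093 | 0.137 |

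For reference, independent tests would give 1 - 0.95³ = 0.143 for three and 1 - 0.95⁴ = 0.185 for four. The nominal level is 0.05.

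**4. The small band.** The smallest |d| that a two-sided t test calls significant is t(0.975; 2n - 2) × √(2/n).

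- n = 204 per arm: 1.966 × 0.0990 = **0.195**.
- n = 51 per arm: 1.984 × 0.198 = **0.39**.

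Both lie below 0.50, so every non-significant result at the planned evaluable numbers, including d = 0, falls in the small band.

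**The case against.** The strongest defence is that the intended reading is clear enough. Sample size names T3 against T0. The mixed model comes first, answers the stated purpose and alone is labelled intention-to-treat. The t tests then sit beside Cohen's d as a visit-by-visit description. The article is condensed, and an analysis plan that is not shown may fix the hierarchy. Much of this stands: a reader might infer that the trial has no intended contrast, and that goes too far. But the article states the t tests as inferential analyses under the same threshold, and it does not call them supportive.

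Other stronger readings are also not supported:

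- **That the trial runs at a 14-16% error rate.** This needs a rule that any win counts, and the protocol states none. About half of the two-sided false positives would also favour control.
- **That there are certainly three t tests.** Study design counts T1 as a follow-up assessment, but the opening of Methods/design and Outcome assessment separate post-intervention from follow-up. With two tests the rate is at most 1 - 0.95² = 0.0975.
- **That the t tests are completer-only and biased.** They are available-case at each visit. The 25% drop-out refers to T0 to T3, and T1 falls only weeks after inclusion. Bias depends on why data are missing. Chance baseline imbalance adds variance but does not bias a randomised comparison.
- **That the raw test is always weaker than the planned model.** The form of the model is not given, and against a plain change contrast this needs r above 0.5.

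The d labels decide nothing, and that d uses raw visit means is an inference from its definition. The missing lower limit is nevertheless in the text.

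**Conclusion.** The point holds in a limited form. The analysis section commits to two kinds of test of the primary outcome at one threshold, does not say which decides, and does not carry forward the powered T3-T0 contrast or its sidedness. The raw t tests are less precise than a baseline-adjusted contrast by a variance factor of 1.33 to 1.96 at r = 0.5 to 0.7, and they may disagree with the model if drop-out depends on earlier scores. The variance factors and the false-positive rates of 10-13% and 14-16% rest on assumed correlations. The false-positive rates also need complete data, three t tests and a claim made on any nominal success, so they show what the wording leaves open and are not the trial's error rate. The labelling fault depends only on the planned numbers and the stated bands.

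**What to change.** In Statistical analyses:

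1. Name the between-arm PAM difference at T3 from the mixed model as the single primary test. Adjust for baseline, either with a common baseline mean across arms or with baseline as a covariate, and state whether the test is one- or two-sided.
2. Take the T1 and T2 differences from the same model as secondary results.
3. Drop the raw t tests for efficacy, or label them descriptive.
4. Give the small band for Cohen's d a lower limit (0.20 is a common convention) and call values below it negligible. State which means and SD enter d.

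The cost is wording. The data, the software and the 51/68/544 calculation stay as they are, and the article reports that inclusion is still under way. Only the sidedness needs some thought. For a raw comparison of 0.5 SD with 51 per arm, power by the normal approximation is 0.81 one-sided and 0.71 two-sided. With 204 per arm it is 0.999 two-sided. The choice therefore matters if the claim is made within each tumour type, and hardly at all if the tumour types are pooled.

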#### Cost-utility analyses

An incremental cost-utility ratio (ICUR) will be calculated to measure the cost per gained QALY. The ICUR will be calculated by dividing the incremental costs by the incremental QALYs using the formula: ICUR = (Costs_intervention_ − Costs_control_)/(QALY_intervention_ − QALY_control_). Total costs will be calculated using a societal perspective, including intervention costs, direct medical costs, direct non-medical costs and indirect non-medical costs. Direct medical and non-medical costs will be calculated by multiplying resource use by integral cost prices as presented in the Dutch Health Care Insurance Board (CVZ) guidelines on cost studies [48]. Indirect non-medical costs will be calculated using the friction cost approach as recommended in the CVZ guidelines [48]. The utility scores linked to the various health states of the EQ-5D [36] will be used to calculate QALYs by weighing the length of time spent in a particular health condition by the utility. Missing data on direct medical, direct non-medical and indirect non-medical costs measured using the cost questionnaire, and utilities measured using the EQ-5D will be imputed using multiple imputation. Because follow-up of the study is less than 1 year, neither costs nor effects will be discounted.

The uncertainty surrounding the ICUR will be assessed using bootstrapping with 5000 replications and projected on a cost-utility plane. In addition, cost-utility acceptability curves will be presented and sensitivity analyses will be performed, focusing on uncertainty around the most important cost parameters. The analysis will be conducted in accordance with the intention-to-treat principle.

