#### Outcome measures on cost-utility

A cost-utility analysis will be conducted; that is, the difference in total 6-month costs between the two arms will be compared with the difference in quality-adjusted life-years (QALYs) based on the 5-dimension EuroQol questionnaire (EQ-5D). The EQ-5D consists of five items measuring problems in five dimensions of quality of life (mobility, self-care, usual activities, pain/discomfort and anxiety/depression). Patients can answer that they have no problems, some problems or extreme problems [35]. The resulting profile of answers (1 of 243 possibilities) can be transformed to a value given by the general public: the EQ-5D index using the Dutch index tariff [36]. Furthermore, a visual analogue scale is included, which represents the patient’s judgment of his or her own health state on a scale from 0 (worst health state) to 100 (best health state).

Direct medical costs (healthcare and medication use), direct non-medical costs (travelling costs and help received from family or friends) and indirect non-medical costs (productivity losses) in the previous 3 months will be measured using an adapted version of the Institute for Medical Technology Assessment Medical Consumption Questionnaire (iMCQ) [37] and Institute for Medical Technology Assessment Productivity Cost Questionnaire (iPCQ) [38] of the Institute for Medical Technology Assessment (iMTA) of Erasmus University Rotterdam (Rotterdam, The Netherlands). In addition, a case report form on healthcare use in the hospital during the study period, including medical specialist visits, day treatment and hospital admission, will be completed using the hospital information system.

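### The ICUR as written has no baseline term, so incremental QALYs are estimated less precisely than the T0 EQ-5D data would allow

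*Protocol article*

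**What the plan says.** All references are to the Protocol article.

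- **Estimator.** Cost-utility analyses states: "The ICUR will be calculated by dividing the incremental costs by the incremental QALYs using the formula", followed by the arm difference in costs divided by the arm difference in QALYs. Outcome measures on cost-utility describes the same contrast: "the difference in total 6-month costs between the two arms will be compared with the difference in quality-adjusted life-years".
- **QALY.** EQ-5D utilities are "used to calculate QALYs by weighing the length of time spent in a particular health condition by the utility". The interpolation rule between visits is not given.
- **Timing.** Outcome assessment: "Cost-utility outcomes are collected at baseline and at 3- and 6-month follow-up". Under Study design, T0 is completed before the second consent and randomisation.
- **Cost recall.** Costs "in the previous 3 months will be measured using an adapted version" of the two iMTA questionnaires, so the T0 questionnaire covers a period before the trial's 6-month window.
- **Balance.** Under Randomisation, the only stratification factor is tumour type. Under Statistical analyses, chi-square, t and Mann-Whitney tests "will be used to analyse whether randomisation resulted in comparable patient groups", with no consequence attached to the result.
- **Uncertainty.** "The uncertainty surrounding the ICUR will be assessed using bootstrapping with 5000 replications", with a cost-utility plane and acceptability curves. Sensitivity analyses are described as "focusing on uncertainty around the most important cost parameters".

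**The concern.** The cost-utility section is specific. It fixes the societal perspective, the price source, the friction cost method, multiple imputation, no discounting and the number of bootstrap replications. At that level of detail, an estimator written as one arm minus the other reads most naturally as a difference of unadjusted arm means.

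For QALYs that choice has a cost. Under the usual area-under-the-curve calculation, the T0 utility, measured before allocation, is itself part of the outcome. Patients who start with higher utility also tend to have higher utility at T2 and T3. Any chance arm difference in T0 utility therefore enters the denominator of the ICUR twice: through its own weight and through correlation. Over half a year the denominator may well be small (the article states no expected gain), and a ratio with a small denominator is sensitive to shifts of this kind. The covariate that would absorb most of this variation is already collected.

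**Working it through.** **The plan's own figure.** The article states no number for the cost-utility analysis, so the arm size comes from Sample size. An exact one-sided t-test at 0.5 SD, alpha 0.05 and power 0.80 needs 50.15, so 51 per arm per tumour type. Then 51 / 0.75 = 68, and 68 × 2 arms × 4 tumour types = 544. This reproduces the plan and gives 68 × 4 = 272 per arm.

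**Assumptions that are not in the article.** Linear interpolation with visits at 0, 3 and 6 months; EQ-5D utility SD 0.15 to 0.25; equal correlation ρ of 0.4 to 0.8 between any two visits; all 272 per arm analysed, with missing values imputed.

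**QALY weights.** Two trapezoids, each 0.25 year wide:

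QALY = 0.25 × (U0 + U2)/2 + 0.25 × (U2 + U3)/2 = 0.125 U0 + 0.25 U2 + 0.125 U3

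**Carry-over of a T0 imbalance.** The regression slope of QALY on U0 is 0.125 + (0.25 + 0.125)ρ = 0.125 + 0.375ρ. The 0.125 is mechanical and the rest is correlation.

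**Variance.** Var(QALY)/SD² = (0.125² + 0.25² + 0.125²) + 2ρ(0.03125 + 0.03125 + 0.015625) = 0.09375 + 0.15625ρ.

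**Gain from adjustment.** R² = slope² / (0.09375 + 0.15625ρ), and the SE ratio (adjusted to unadjusted) is √(1 − R²).

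**Chance imbalance.** The SE of the T0 utility difference is SD × √(2/272) = 0.0129, 0.0171 and 0.0214 for SD 0.15, 0.20 and 0.25. Multiplying by the slope gives the shift in the QALY difference from a one-SE imbalance:

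| ρ | Slope | R² | SE ratio | Shift, SD 0.15 | Shift, SD 0.20 | Shift, SD 0.25 |
|---|---|---|---|---|---|---|
| 0.4 | 0.275 | 0.48 | 0.72 | 0.0035 | 0.0047 | 0.0059 |
| 0.6 | 0.350 | 0.65 | 0.59 | 0.0045 | 0.0060 | 0.0075 |
| 0.8 | 0.425 | 0.83 | 0.42 | 0.0055 | 0.0073 | 0.0091 |

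The SE ratio does not depend on the SD or the arm size.

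**Scale.** A utility gain of 0.02 held at both T2 and T3 is worth 0.02 × 0.375 = 0.0075 QALY, the same order as the shifts above.

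**Effect on the ratio (illustration).** Assume a cost difference of 200 and a true QALY gain of 0.010, so the ICUR is 20,000. At ρ = 0.6, a T0 imbalance of ±0.02 (0.02 / 0.0171 = 1.2 SE at SD 0.20) moves the QALY difference by 0.35 × 0.02 = 0.007. The ICUR becomes 200 / 0.017 ≈ 11,800 or 200 / 0.003 ≈ 66,700. At ρ = 0.4 the pair is about 12,900 and 44,400; at ρ = 0.8 it is about 10,800 and 133,000.

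**Would the comparability tests flag it?** At SD 0.20 the T0 difference must reach about 1.96 × 0.0171 = 0.034 for p < 0.05. An imbalance of 0.02 would not be flagged.

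**Costs.** T0 costs cover the three months before baseline and have weight zero in the 6-month total. Adjustment helps only through correlation r, with SE ratio √(1 − r²): 0.95, 0.87 and 0.71 for assumed r of 0.3, 0.5 and 0.7.

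**The case against.** There are four points on the other side.

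**The article never calls the increments unadjusted.** A reader might infer that the trial has decided on raw arm differences. The documents do not say that. The formula is the general definition of an ICUR, and regression-adjusted increments satisfy it. A full protocol or analysis plan, not shown here, may specify them. This stands as a limit on the wording: an unadjusted difference is the natural reading of a detailed section, not a stated choice.

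**There is no bias.** A reader might also infer that baseline imbalance makes the planned result invalid. It does not. Under 1:1 randomisation the unadjusted increments are unbiased, and chance imbalance is part of the sampling error that the bootstrap reflects. At SD 0.20 and ρ = 0.6 the unadjusted SE of the QALY difference is 0.0074, which splits into 0.0060 from T0 imbalance and 0.0044 from the rest: √(0.0060² + 0.0044²) = 0.0074. This stands in full. What remains is that the larger component is avoidable, and that the bootstrap cloud is centred on whatever point estimate the imbalance produced.

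**Costs are different.** It would be tempting to say that baseline cost imbalance feeds directly into the ICUR as utility does. The recall window rules that out, since T0 costs are not in the numerator.

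**The size rests on assumed inputs.** SD, correlation, QALY gain and interpolation rule are all absent from the article. This stands, which is why ranges are shown. The direction of the precision gain needs only a positive correlation between visits.

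**Conclusion.** The point holds as a recommended improvement to the estimator. As written, the cost-utility analysis makes no use of T0 utility as a covariate, although it is collected, is part of the QALY under linear interpolation, and is likely to be strongly prognostic. Adjustment would bring the SE of the QALY difference to 0.72 to 0.42 of its unadjusted value for correlation 0.4 to 0.8. At 0.6 the ratio is 0.59, equivalent to 1 / 0.59² ≈ 2.9 times the sample for that contrast. A one-SE chance imbalance shifts the unadjusted QALY difference by about 0.0035 to 0.009 with 272 per arm and SD 0.15 to 0.25. The cost side gains less (SE ratio about 0.95 to 0.71), through correlation alone. The planned analysis would be valid but inefficient.

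**What to change.** In Cost-utility analyses, state that:

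1. incremental QALYs are estimated by regression on arm, T0 utility and tumour type;
2. incremental costs are estimated by regression on arm, T0 three-month costs and tumour type;
3. both regressions are refitted within each of the 5000 bootstrap samples, and the ICUR, plane and acceptability curve are built from the adjusted increments;
4. the unadjusted increments are reported as a sensitivity analysis.

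The interpolation rule for QALYs should be named in the same place. The cost is a few lines of text and code, with no new data. If a fuller protocol or analysis plan already specifies this adjustment, one clarifying sentence is enough. The change should be fixed before unblinded cost or utility data are examined, so that the choice of estimator cannot depend on the observed imbalance.
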